#### Outcome-parameter

Outcome parameters were defined considering best available evidence, legal regulations and feasibility. According to our two scientific hypotheses two groups of outcome parameters were defined: "outcome parameters I" for the comparison of the DMP groups and "outcome parameters II" for the comparison of DMP and routine care. This differentiation of the outcome parameters is essential because in the control group availability of patient data will be limited to process indicators only. The outcome parameters are displayed in Table 1.

**Table 1 T1:** Primary and secondary outcome parameters

**OUTCOME PARAMETERS I**	**OUTCOME PARAMETERS II**
**DMP 1 vs. DMP 2**	**DMP 1 vs. CG**
***Primary outcome parameter***	***Primary outcome parameter***

Proportion of patients achieving target values for HbA1c and RR according to the legal regulations (10)	Proportion of patients with prescriptions for antidiabetic, antihypertensive and lipid-lowering drugs

***Secondary outcome parameters***	***Secondary outcome parameters***

Proportion of patients with prescriptions for antidiabetic, antihypertensive and lipid-lowering drugs	----
Proportion of patients with referrals to ophthalmologists, specialists for diabetology and diabetic feet	Proportion of patients with referrals to ophthalmologists, specialists for diabetology and diabetic feet
Proportion of patients referred to a patient education training for diabetes and hypertension	Proportion of patients referred to a patient education training for diabetes and hypertension
Proportion of patients with severe complications (amputation, dialysis etc.)	Proportion of patients with severe complications (amputation, dialysis etc.)
Proportion of patients with > 2 hospitalizations in the last 6 months	Proportion of patients with > 2 hospitalizations in the last 6 months
Consultation rate	Consultation rate
Days of incapacity to work	Days of incapacity to work
Mean differences of HbA1c, RR, BMI and glomerular filtration rate	---
SCORE risk chart (RR, cholesterol, smoking status, age, gender)	---
Drop out rate from the DMP	---

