**Methods/Design:**

The study is three-armed: a prospective cluster-randomized comparison of two interventions (DMP 1 and DMP 2) against routine care without DMP as control group. In the DMP group 1 the patients are treated according to the current situation within the German-Diabetes-DMP. The DMP group 2 represents diabetic care within ideally implemented DMP providing additional interventions (e.g. quality circles, outreach visits). According to a sample size calculation a sample size of 200 GPs (each GP including 20 patients) will be required for the comparison of DMP 1 and DMP 2 considering possible drop-outs. For the comparison with routine care 4000 patients identified by diabetic tracer medication and age (> 50 years) will be analyzed.

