#### Sample size calculation

Sample size calculations for cluster randomized trials differ from sample size calculations for common RCTs requiring a larger number of patients. Based on the main outcome parameters we performed a power calculation with the Cluster Randomization Sample Size Calculator ver.1.02 of the University of Aberdeen on the basis of an ICC of 0,05. Considering possible drop-outs a sample size of 200 GPs will be required (each GP including 20 patients).

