#### Selection of participants

500 GPs in Rheinland-Pfalz and 500 GPs in Sachsen-Anhalt participating in the Diabetes-DMP will be recruited by an invitation letter giving information about the study project. From those who will accept to participate, 100 GPs will be randomized in the DMP group 1 and 100 in the DMP group 2. All patients with a type 2 diabetes out of these practices insured at the general regional health funds (*Allgemeine Ortskrankenkassen = AOK*) and participating in the DMP will be included in the study then. Incomplete participation in the interventions will be an exclusion criterion in the DMP group 2.

For the control group 4000 AOK patients out of practices not participating in the DMP will be detected through diabetes tracer medication and age (> 50 years) and will be matched. Participation in a DMP offered by another health fund is an exclusion criterion in the control group.

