## Discussion

There are specific difficulties in evaluating the effectiveness of complex interventions such as disease management programs [19], particularly, in our case that implementation process has already started [15]. At the moment it is not conceivable to which phase of the implementation process the DMP actually has preceded. However, the DMP group 2 represents an ideal implementation of the DMP within the scope of the German law regulation.

To adapt the evaluation design to the real conditions of diabetes care in Germany at the moment, but also to consider the ongoing implementation process we have chosen the design of a prospective randomized-controlled comparison of the two DMP groups embedded in the quasi-experimental design of a controlled before-after study with a blinded control group. The quasi-experimental design is predetermined because allocation to the control group can not be perfomed randomly and because baseline values for patients participating in the DMP have not been documented.

A fully experimental design with a randomized control group was rejected by the authors, because this could create an artificial care situation. That is informing patients and GPs of the control group about the study and probably asking for completing any questionnaires would introduce an enormous bias.

According to the theoretical model for design and evaluation of complex interventions by Campbell et al the presented study can be assigned to phase III and IV (15, 20). However, pilot projects have shown that an observation period of 24 months will be too short to show significant differences in severe clinical endpoints (i.e. amputations, diabetic renal insufficiency, cardio-vascular events). Therefore it was decided to have a combination of HbA1c and blood pressure as primary endpoint in the randomized part of the trail and prescriptions in the quasi-experimental part of the trial.

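### In DMP 1 vs. control only, an over-50 rule that binds just the controls lets age and employment mix enter the difference in days of incapacity to work

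*Protocol article*

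**What the plan says.** All places are in the protocol article.

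- Outcome-parameter, Table 1: "Days of incapacity to work" is a secondary outcome in both columns, DMP 1 vs. DMP 2 and DMP 1 vs. CG. No denominator, time unit or summary measure is attached to it.
- Selection of participants, DMP groups: "All patients with a type 2 diabetes out of these practices insured at the general regional health funds" and enrolled in the DMP are included. No age limit is given. The same rule covers both DMP arms, and "100 GPs will be randomized in the DMP group 1 and 100 in the DMP group 2".
- Selection of participants, control group: the 4000 AOK patients from practices outside the DMP "will be detected through diabetes tracer medication and age (> 50 years) and will be matched". The matching variables are not listed. The abstract (Methods/Design) repeats the age rule: "4000 patients identified by diabetic tracer medication and age (> 50 years) will be analyzed".
- Discussion: "allocation to the control group can not be perfomed randomly", and the randomised comparison is "embedded in the quasi-experimental design of a controlled before-after study with a blinded control group".

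Employment status is not mentioned anywhere in the article.

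**The concern.** A day of incapacity to work can arise only in someone who has work. Among the outcomes listed for DMP 1 vs. control, this one is therefore especially sensitive to the share of each group that is of working age and employed.

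The selection rules act on that share from one side only. Controls aged 50 or under are excluded by design, while DMP patients of that age are kept. Randomisation does not protect this comparison. If the DMP 1 group contains more people of working age, it can accumulate more days of incapacity per patient with identical care. The distortion runs against the programme: younger patients would make DMP 1 look worse than routine care. At stake is the interpretation of one of six secondary outcomes in this comparison. No primary outcome and no sample size depends on it.

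**Working it through.** **The plan's own figures.** The article gives no figure for this outcome: no expected days, age distribution or employed share. Its only calculation, 200 GPs with 20 patients each "on the basis of an ICC of 0,05", concerns DMP 1 vs. DMP 2 and has no bearing here. What follows illustrates the mechanism on assumed inputs.

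**Assumed inputs**

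- *w*, share employed among patients over 50: 0.20 to 0.40
- *v*, share employed among patients aged 50 or under: 0.60 to 0.80
- *y*, share of DMP 1 patients aged 50 or under: 0 to 0.20 (zero among controls, by the selection rule)
- *d*, days per employed patient: the same in both groups and at all ages, so care has no effect
- analysis by a mean over all patients, which Table 1 neither states nor excludes, with no age matching

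**Formulas**

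- Control mean = *w* × *d*
- DMP 1 mean = [*y* × *v* + (1 − *y*) × *w*] × *d*
- Ratio = 1 + *y* × (*v*/*w* − 1); *d* cancels

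**Results** (range from *v* = 0.60 to *v* = 0.80)

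| | *w* = 0.20 | *w* = 0.30 | *w* = 0.40 |
|---|---|---|---|
| *y* = 0 | 1.00 | 1.00 | 1.00 |
| *y* = 0.05 | 1.10-1.15 | 1.05-1.08 | 1.03-1.05 |
| *y* = 0.10 | 1.20-1.30 | 1.10-1.17 | 1.05-1.10 |
| *y* = 0.20 | 1.40-1.60 | 1.20-1.33 | 1.10-1.20 |

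Worked example with *y* = 0.10, *v* = 0.80, *w* = 0.30, *d* = 10: the DMP 1 employed share is 0.10 × 0.80 + 0.90 × 0.30 = 0.35. The means are 3.5 and 3.0 days, ratio 3.5/3.0 = 1.17.

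**Same age rule in both groups.** With *y* = 0 on both sides the age-rule part of the ratio is 1.00. A denominator of employed patients also gives 1.00, provided days per employed patient do not vary with age.

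**Before-after contrast.** Suppose baseline days are available in both groups, a share *r* of all patients over 50 stops working during observation, nobody aged 50 or under does, and *d* is stable. The control mean falls by *r* × *d* and the DMP 1 mean by (1 − *y*) × *r* × *d*. The difference in change is *y* × *r* × *d*. In the worked example this is 0.10 × *r* × 10 = *r* days. Since *r* cannot exceed *w* = 0.30, it is at most 0.3 days, against 0.5 days without differencing. Differencing reduces the distortion but need not remove it.

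**DMP 1 vs. DMP 2.** One age rule and random allocation make *y*, *v* and *w* equal in expectation, so the expected ratio without an effect of care is 1.00. In an all-patient mean, non-workers shrink a true difference. An assumed 4 days among workers becomes 4 × 0.35 = 1.4 days at 35% employed, and 0.8 to 2.0 days at 20% to 50%.

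**The case against.** The strongest objection is that Table 1 gives only a label. It does not say that the outcome is averaged over all patients or that non-workers count as zero, and a per-worker rate would fit the table equally well. An article may leave such definitions to the full protocol or SAP. This stands: the missing denominator is not a finding by itself. What the article does fix is the one-sided age rule.

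Second, controls are to be matched, and if age is a matching variable the age-rule imbalance could vanish. This stands in part. DMP patients aged 50 or under can have no control of the same age, so matching solves the problem only if those patients also leave the comparison. The article says that all DMP patients are included and does not say that unmatched ones are dropped.

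Third, the comparison is described as controlled before-after, which offsets a stable difference in employment mix. This also stands in part. The Discussion says that baseline values for DMP participants have not been documented, although the Timeframe section plans pre-data collection and claims-based days might be available. Even then, retirement over 24 months can proceed at a different pace in the two groups.

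A reader might also infer that the randomised comparison is biased. It is not: the age rule is shared there, and dilution is the only consequence.

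**Conclusion.** The point holds for DMP 1 vs. control only, and it is minor. As specified, the groups follow different age rules in a non-randomised comparison, and this outcome depends strongly on working age. A difference can therefore mix age and employment with any effect of care.

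The size cannot be derived from the article. The range of 1.00 to 1.60 rests on the assumed shares, an all-patient mean, no age matching and no before-after adjustment. It includes no distortion at all.

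Two stronger readings are tempting and not supported. A reader might infer that the outcome measures who is still working and not the care given; at most it mixes the two. A reader might also take one pair of employed shares, say 35% and 25% at 20 days per worker, and report 7.0 vs. 5.0 days as a 40% spurious excess. Those inputs have no source in the article. For the age rule alone to raise 25% to 35%, between (0.35 − 0.25)/(0.80 − 0.25) = 18% and (0.35 − 0.25)/(0.60 − 0.25) = 29% of DMP 1 patients would have to be aged 50 or under.

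**What to change.** In the DMP 1 vs. control comparison, apply the over-50 rule to both groups, or match on age within that range, and state the matching variables. Define days of incapacity among patients recorded as employed at the start of observation.

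In the main analysis, do not end person-time at later retirement or job loss. Leaving work may itself be related to the disease and its care, so stopping follow-up there would condition on an event after the start of observation. It could be examined as a sensitivity analysis.

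The cost is a smaller denominator for one secondary outcome and an employment-status field from the AOK. The article says that all data come from the AOK but does not say that this field is available, so that is assumed. One limitation remains: patients may have joined the DMP before observation starts, so employment at that date is not strictly a pre-programme characteristic. DMP 1 vs. DMP 2 needs no change in its age rule; using the employed denominator there would only reduce dilution.

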### Intervention

The minimum requirements for the Diabetes-DMP are regulated by law and defined in the RSAV [10]. According to the legal regulations the intervention in the DMP1 group comprises consultations at 3- or 6-months intervals. During these consultations a detailed diabetes-specific anamnesis and physical examination incl. taking blood pressure and an analysis of HbA1c are carried out. Furthermore agreements are made concerning further treatment, e.g. target values for HbA1c and blood pressure and participation on patient education programs for diabetes or hypertension. All medical findings as well as the current medication have to be documented within structured, standardized documentation sheets at each consultation. If required a referral to a specialist (e.g. ophthalmologist) will be arranged. Furthermore the GPs get a special diabetes-handbook including current, evidence-based information about diabetes therapy. The GPs participating in the DMP1 group will receive no additional intervention.

There are major difficulties introducing new evidence into general practice requiring comprehensive implementation support at different levels (patients, doctors, practice team) [17,18]. Therefore, in the DMP 2 group implementation support at the level of doctors and practice team will be provided. In addition to the clinical interventions at patients level in the DMP group 1 several components aiming at optimizing the implementation process are provided in this group (= implementation interventions) (Table 2).

**Table 2 T2:** Implementation Interventions in DMP 2 group

**Interventions**	**Description**
Interactive quality circle meetings	During these meetings all aspects of evidence based treatment of diabetes in a primary care setting will be discussed (2 × per year).
Educational meetings for medical assistants	During these meetings medical assistants will be supported in finding individual strategies for optimal implementation of the DMP in their practices (2 × per year).
Outreach visits	During these meetings individual problems within the implementation process of the DMP will be discussed with the GP and the assistant team (1 × per year)
Homepage with "best practice" examples	Detailed information for the praxis team about Diabetes-DMP incl. case studies via internet (electronic individual feedback)

The control group represents routine care without DMP. There will be no intervention at all.

### Timeframe of the study

The study team will start to invite GPs at the end of September 2005. After receiving a written declaration of their willingness to participate in the study and to accept random assignment to the different groups GPs will be randomized.

Patient inclusion and pre-data collection will start in 2005. The observation period will be 24 months.

### Description of risks

Since the interventions aim at the evidence based improvement of skills of GPs and practice teams serious risks or undesired effects for patients are not to be expected. There are no specific risks related to the study.

### Patient informed consent

Previous to DMP participation patients already receive written and oral information about the content and extent of the DMP by their treating GPs, i.e. about potential benefits for their health and potential risks. Furthermore, patients are informed that DMP data including medical data will be analyzed. In case of acceptance they have to sign a special DMP participation form.

### Ethical principles and vote of the ethics committee

The study is being conducted in accordance with medical professional codex and the Helsinki Declaration as of 1996 as well as the German Federal Data Security Law (BDSG). DMP participation of patients is voluntary and can be cancelled at any time without provision of reasons and without negative consequences for their future medical care.

The study protocol was approved by the ethics committee of the University of Heidelberg in April 2005 (Approval-Nr. 098-2005). Furthermore the evaluation of the DMP is regulated by law in the Fifth Book of Social Code (§137 f. Abs. 4 SGB V).

### Data security/disclosure of original documents

The patient names and all other confidential information fall under medical confidentiality rules and are treated according to German Federal Data Security Law (BDSG).

Data management will be performed by the AQUA-Institute, Goettingen. All study related data are stored on a protected central server. Only direct members of the internal study team can access the respective files. Intermediate and final reports are stored at the office of the Department of General Practice and Health Services Research at the Heidelberg University Clinic.

## Discussion

There are specific difficulties in evaluating the effectiveness of complex interventions such as disease management programs [19], particularly, in our case that implementation process has already started [15]. At the moment it is not conceivable to which phase of the implementation process the DMP actually has preceded. However, the DMP group 2 represents an ideal implementation of the DMP within the scope of the German law regulation.

To adapt the evaluation design to the real conditions of diabetes care in Germany at the moment, but also to consider the ongoing implementation process we have chosen the design of a prospective randomized-controlled comparison of the two DMP groups embedded in the quasi-experimental design of a controlled before-after study with a blinded control group. The quasi-experimental design is predetermined because allocation to the control group can not be perfomed randomly and because baseline values for patients participating in the DMP have not been documented.

A fully experimental design with a randomized control group was rejected by the authors, because this could create an artificial care situation. That is informing patients and GPs of the control group about the study and probably asking for completing any questionnaires would introduce an enormous bias.

According to the theoretical model for design and evaluation of complex interventions by Campbell et al the presented study can be assigned to phase III and IV (15, 20). However, pilot projects have shown that an observation period of 24 months will be too short to show significant differences in severe clinical endpoints (i.e. amputations, diabetic renal insufficiency, cardio-vascular events). Therefore it was decided to have a combination of HbA1c and blood pressure as primary endpoint in the randomized part of the trail and prescriptions in the quasi-experimental part of the trial.
